**Fig 1 pone.0294199.g001:**
[figure not shown]
Chart of trial design.

## Materials and equipment

The platform used during the training will be an immersive VR apparatus available at the Department of Geriatrics and Cardiovascular Medicine of the Istituto Auxologico Italiano: Cave Automatic Virtual Environment (CAVE). This system is composed of a room-sized cube in which four stereoscopic projectors (Full HD 3D UXGA DLP) are used to cast a three-dimensional image of the Virtual Environment (VE) onto three walls and the floor. In particular, there are three retro-projected screens (frontal, right, and left) and a direct-projection screen (floor screen). Four infrared cameras are employed to monitor any movements made by 3-D glasses. Active goggles combine the projected images for the right and left eyes to enable the feeling of depth. A tracking optical system is included in CAVE in addition to the visualization tools (VICON). The virtual scene in the CAVE is encoded with depth information, which is recovered and delivered to the eyes via 3-D glasses. The user has the impression that he/she is still moving around the object in 360 degrees because of the different images and viewpoints. As the user moves their head, the image almost spins in real time. An asymmetrical set of markers on both CAVE goggles and an Xbox joystick enable the retrieval of their position and heading in the environment. These data bits are utilized to enable the Xbox joystick to be used as a pointer for interfacing with 2D interactable components (such as buttons) in the CAVE and to modify the user’s point of view, respectively. A cluster system made up of two HPZ620 Graphics Workstations and an Nvidia Quadro K6000 GPU with specific Quadro Sync cards manages all the CAVE features. This technology ensures a true-to-life experience.

Different tools were created to perform several activities in the Cave. Training will be developed based on existing tools, enriching and combining them to create a new training protocol. It will involve different dual-task exercises: the Positive Bike, Rocks, and the Supermarket. They will be proposed in a randomized order within subjects.

*Positive Bike*. It is an innovative immersive tool proposed by Pedroli et al. (2019a) [19] which consists of a stationary bike placed inside the CAVE in which patients cycle and keep their cycling velocity steady (motor task); concurrently they have to recognize target objects between distractors (cognitive task). The therapist decided the exercise parameters (e.g. time between targets presentation, the target to select, bike velocity) in each session.*Rocks*. The exercise, developed by Pedroli et al (2019) [19], originates to train balance. Patients are immersed in a virtual environment resembling a straight dirt road and have to avoid rocks (motor task) they encounter on the way, moving their body in the right or left direction. We will add a cognitive part: while moving subjects will have to declare their direction (e.g. they will say ‘right’ if rocks move on the right and ‘left’ if they move on the left).*Supermarket*. This exercise takes place in a virtual supermarket, as proposed by Pedroli et al. (2018) [32]. It aims to train executive functions: users have to move in the shop using an Xbox controller and they must buy several products following precise rules. Ten different tasks with increasing difficulty are available. To create a dual-task, while shopping, we will add a motor task consisting of a walk in place with a metronome.

All cited VEs were created utilizing Unity 3D and the MiddleVR Unity plug-in. This plug-in enables the communication between the Unity application and all the CAVE system components, allowing for the projection of scenes onto the CAVE walls and the use of motion data from the VICON system as inputs. The parts of the system are highlighted in Fig 2.

**Fig 2 pone.0294199.g002:**
[figure not shown]
A schematic representation of the VR system, CAVE, with the stationary bike.

## Participants

Participants will be volunteers of both sexes, aged 65 or over (without maximum age limitation), and with Parkinsonian Syndromes as classified by Williams and Litvan (2013) [31]. The eligibility criteria will require the participants to have an MMSE [33,34] score between 30 and 24 and all participants will have normal or corrected-to-normal vision. Exclusion criteria will be invalidating internist, psychiatric, neurological conditions, presence of depression or anxiety without medications and hemianopsia or hemiplegia, severe physical or functional limitations impeding physical activity, and recurrent vertigo. The presence or absence of these criteria will be assessed during the initial clinical assessment performed by a physician. The final sample will be composed of 45 patients; to achieve this goal, at least 50 subjects will be assessed. To evaluate the size of the samples, we used a Sample Size Calculation (Power Analysis) using the software GPower*3. Based on data from Killane et al. [22], with an effect size of 0.43, alpha of 0.05, and 80% power and we estimated the minimum of subjects to be included in the rehabilitation experiment.

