## Data analysis

We will realize a mixed design trial (2x3) with population training (VR vs. TAU) as a between variable and assessment of training effect (pre-test, post-test, and follow-up) within variables. A Windows Excel sheet will be used to organize all the data related to demographic and assessment information and an identification code will be assigned to each participant to ensure anonymity of the data. A mixed ANOVA will be performed to investigate interaction effects between and within variables.

Moreover, we will analyze the accuracy during DT training to verify possible correlations with the accuracy measure in the assessment part at t0 and t1. The objective will be to examine if traditional tests reflect trained abilities.

Moreover, we will propose an innovative approach of ML in the rehabilitation field, to estimate the TEP from the collected data during the DT VR experience. Based on our research question and available data we will use a classification algorithm to create a model; we will train and test the model using data to forecast which motor or cognitive parameters are more predictive for the future maintenance of any improvements obtained, based on the model proposed by Shi and colleagues (2019) [44]. We will use one of the best programs for ML analysis, such as Python.

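### The 80% power quoted for 45 patients fits a one-group paired test or a between-arm difference of 0.86 SD, and neither is the planned group-by-time comparison at 0.43

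*Protocol article*

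**What the plan says.** The Participants section gives the target and the calculation together. On numbers: "The final sample will be composed of 45 patients; to achieve this goal, at least 50 subjects will be assessed". On method: "we used a Sample Size Calculation (Power Analysis) using the software GPower*3". The inputs are "with an effect size of 0.43, alpha of 0.05, and 80% power", with the effect size taken from an earlier published study. The section does not say whether 0.43 is d, dz or f, which test was chosen in the software, which outcome it refers to, or whether the test is two-sided.

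The Experimental design section randomises patients to two arms, VR dual-task training or treatment as usual, with assessments at t0, t1 and t2. The Data analysis section states: "We will realize a mixed design trial (2x3) with population training (VR vs. TAU) as a between variable". The three assessments are the within-patient factor, and a mixed ANOVA is to examine the interaction.

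**The concern.** The trial asks whether VR dual-task training does better than usual treatment. A power statement should therefore describe the chance of detecting a stated difference between the arms with the planned test. Most readers will take an effect size of 0.43 in a two-arm trial as a standardised mean difference, a small-to-moderate effect. Forty-five patients in two arms cannot give 80% power for that in a simple comparison.

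The reading of a null result is at stake. If the article is taken to promise 80% power at 0.43, a non-significant interaction will look like evidence that VR has no worthwhile advantage. On the d reading, the trial would have missed a true difference of that size more often than not.

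**Working it through.** **Inputs.** From the Participants section: effect size 0.43, alpha 0.05, power 80%, final N = 45. From Experimental design and Data analysis: two randomised arms, three visits, mixed ANOVA interaction. Assumed because not stated: two-sided tests, allocation 22/23, and a correlation between repeated measures of 0 to 0.8.

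**1. Reproducing the 45.**

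- *Paired t-test, dz = 0.43.* Noncentrality = 0.43 × √45 = 2.885 on 44 df, critical t = 2.015. Power is 80.5% at n = 45 and 79.6% at n = 44, so 45 is exactly the minimum.
- *Two-group one-way ANOVA, f = 0.43.* λ = f² × N = 0.1849 × 45 = 8.32 on 1 and 43 df, critical F = 4.07. Power is 80.5% at N = 45 and 79.6% at N = 44, so 45 is again the minimum (46 with equal arms). With two equal groups d = 2f, so this is d = 0.86.

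**2. Two-sample comparison with d = 0.43.** Noncentrality = 0.43 × √(22 × 23/45) = 1.442 on 43 df, critical t = 2.017.

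| Setting | Power |
|---|---|
| 22 v 23, two-sided | 29.1% |
| 22 v 23, one-sided | 41.1% |
| 25 v 25, two-sided | 31.9% |
| 86 v 86, two-sided | 80.1% |

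For 80% power, 86 per arm (172 in total) would be needed. With 22/23, the smallest difference that has 80% power is d = 0.855.

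**3. The planned interaction.** The software's default routine uses λ = f² × N × m/(1 − ρ) with m = 3 visits. At ρ = 0.5 it gives a minimum N of 11 for f = 0.43 and 37 for f = 0.215 (12 and 38 with equal arms). With λ = f² × N instead, f = 0.43 gives 72% power at N = 45. None of these settings yields 45.

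**4. Interaction power when the arms differ by 0.43 SD at t1 and t2 and are equal at t0.** The between-arm differences over the visits are 0, 0.43 and 0.43, with mean 0.287. Their deviations from that mean are −0.287, 0.143 and 0.143. Each arm carries half of each deviation. Averaging the squares over the six cells gives f² = 0.43²/18 = 0.01027, so f = 0.101. Then λ = 0.01027 × 45 × 3/(1 − ρ) = 1.387/(1 − ρ) on 2 and 86 df, critical F = 3.10.

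| Assumed ρ | λ | Power |
|---|---|---|
| 0 | 1.39 | 16% |
| 0.3 | 1.98 | 22% |
| 0.5 | 2.77 | 29% |
| 0.7 | 4.62 | 46% |
| 0.8 | 6.93 | 63% |

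Power does not reach 80% anywhere in this range.

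**The case against.** The strongest reply is that the article never calls 0.43 a standardised mean difference. The planned analysis is an ANOVA, and the named software's ANOVA routines take Cohen's f. With f = 0.43, 45 patients do give 80.5% power for a two-group VR-versus-TAU comparison. On that reading f = 0.43 and d = 0.86 are one effect on two scales, and nothing was miscalculated. This stands. A reader might infer that the trial simply has 29% power, or that the authors used a paired test by mistake. The documents support neither, because the two-group F test gives the same 45 and the source study is not available here to settle the metric.

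It is also fair that 29% is the power of an unadjusted single-visit t-test and not of the planned interaction. One might add that 37 or 38 patients suffice for the interaction at f = 0.215, the value of d/2 for d = 0.43. That does not rescue 0.43 SD. An interaction f of 0.215 corresponds to 0.215 × √18 = 0.91 SD at both later visits, whereas 0.43 SD at both visits is only f = 0.101.

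Finally, the article is condensed, and a fuller protocol may hold the missing inputs. That excuses brevity. It does not remove the mismatch, because the article prints both the result of the calculation and the analysis, and the routes found to 45 do not lead to that analysis.

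The f reading leaves two points open. It sizes the trial for a 0.86 SD advantage over an active comparator, which a reader who sees 0.43 would not guess. It is also a one-way between-group test. For arms 0.86 SD apart at t1 and t2, λ is four times the values in the last table, and interaction power is 53%, 70%, 84%, 97% and above 99% at the same five correlations. Whether the planned test reaches 80% thus depends on a correlation that the article does not state.

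**Conclusion.** Wrong as written: the stated power is not that of the planned comparison at the effect it appears to cite. On the two readings that reproduce 45, the quoted 80% belongs either to a one-group pre-post test or to a between-arm difference of 0.86 SD. Power for VR versus TAU at a single visit is about 29% if 0.43 is d and about 80% if it is f. Interaction power for arms 0.43 SD apart at t1 and t2 is about 16% to 63%.

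These figures assume two-sided alpha 0.05, 22/23 analysed, equal arms at t0, and one common correlation of 0 to 0.8 between visits. They do not show that the sample size was derived by the wrong test, nor that 45 patients are too few for every effect of interest.

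**What to change.** Keep N = 45 and replace the power sentence with one tied to the randomised contrast, for example:

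> *With 45 analysed patients (22/23) and two-sided alpha 0.05, the trial has 80% power for a between-arm difference of about 0.86 SD at one visit, unadjusted.*

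In the same place, name the outcome, the test, the metric of the 0.43 (d, dz or f), and the correlation assumed for the interaction. Print the 29% figure only if 0.43 was meant as a between-arm standardised difference. Label any baseline-adjusted figure as resting on an assumed correlation. Describe the trial as preliminary for smaller effects.

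The change is to wording only and needs no extra patients. Its cost is a stated detectable difference that looks less favourable than the present sentence.

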## Outcome measure

Participants will be assessed to provide information regarding their motor and cognitive abilities, as well as their capacity to perform the mentioned actions simultaneously. We will include evaluation scales related to the functional aspects such as the Tinnetti Balance Scale, the Equiscale, and the Time Up and Go Test (TUG). The Tinetti Balance Scale [35] is the gold standard scale for balance evaluation. It is a simple clinical test consisting of 14 items with a score out of 28. The therapist evaluates patients’ performance in some activities concerning balance, gait, and risk of falling (i.e. standing up, walking, standing down, etc.). The higher the score, the better the performance. The Equiscale [36] includes three subdomains of standing up, resistance to external perturbations, and resistance to self-induced perturbation in a real-life performance, for example, the therapist evaluates the ability to lean forward, sit up, etc. The Timed Up and Go Test (TUG) [37] examine balance, gait speed, and functional abilities required to performance of basic activities of daily living; it measures the time that the subject takes to get up from a standard chair, walk three meters, turn around and go back to sitting down. The highest the time the worse the performance. The optimal cut-off value would be considered from 10 to 33 seconds.

We will also evaluate cognitive domains; the general cognitive status with the MMSE and the executive functions domain with the Frontal Assessment Battery (FAB), the Tower of London (ToL), the Trail Making Test (TMT), and the Stroop Test. The MMSE [33,34] is a brief test that screens the global functioning including temporal and spatial orientation, memory, attention, language, and apraxia. FAB [38] is a screening test composed of six cognitive and behavioural tasks: similarities, phonological verbal fluency, motor series, conflicting instructions, Go-No Go task, and prehension behaviour. The score ranges from 0 to 18. The ToL [39] is traditionally used to assess strategic reasoning, problem-solving, and mental planning in clinical populations. The task consists of moving tree beads to reproduce the target configuration; time and accuracy are evaluated. The TMT [40] measures attention and ability of set-shifting; it is composed of two parts: the first (TMT A) is a searching task, and the second part (TMT B) requires shifting in searching alternatively numbers and letters. During the performance, time is evaluated: the highest time the worst score. The Stroop Test [41] is designed to test the capacity to inhibit cognitive interference, which happens when processing one sensory characteristic interferes with processing another at the same time. It is composed of three parts, for each one the person is instructed to read respectively all the words, colors, and color ink as quickly as possible. A trained physiotherapist and psychologist will perform the assessment to exclude the low reliability of the data.

The ability to engage in both motor and cognitive tasks will be evaluated with the motor and cognitive Time Up & Go Test (TUG) [42] and the Walking and Remembering Test (WART) [42]. Motor and cognitive TUG consists of the previously described motor performance with an adjunct cognitive part requiring the patient to count backward by threes while walking. Similarly, the WART evaluates single and dual-task performance: working memory task while walking. Patients had to walk at their fastest safe speed along a path in both single and dual-task (simultaneous digit span task) conditions. Average walking time was considered.

At last, quality of life will be evaluated using the Italian validation of the Parkinson’s Disease Questionnaire (PDQ-39) [43]. Outcomes information are included in Table 1.

**Table 1 pone.0294199.t001:** Outcome measurements.

Test	Outcomes information
*Motor*	
Tinnetti Balance Scale	Balance
Equiscale	Standing and resistance to external and self-induced perception
TUG	Mobility
*Cognitive*	
MMSE	General cognitive status
FAB	Screening of executive function
ToL	Reasoning and problem-solving
TMT	Attention and set-shifting
Stroop Test	Cognitive flexibility and sensitivity to interference
*Dual-task ability*	
Motor and cognitive TUG	Balance and executive functions
WART	Gait and working memory
**Questionnaire**	**Outcomes information**
PDQ-39	Quality of life

Moreover, we will consider outcome variables provided by the CAVE system during the DT training such as the time, accuracy, velocity, etc. performing each exercise.

## Data analysis

We will realize a mixed design trial (2x3) with population training (VR vs. TAU) as a between variable and assessment of training effect (pre-test, post-test, and follow-up) within variables. A Windows Excel sheet will be used to organize all the data related to demographic and assessment information and an identification code will be assigned to each participant to ensure anonymity of the data. A mixed ANOVA will be performed to investigate interaction effects between and within variables.

Moreover, we will analyze the accuracy during DT training to verify possible correlations with the accuracy measure in the assessment part at t0 and t1. The objective will be to examine if traditional tests reflect trained abilities.

Moreover, we will propose an innovative approach of ML in the rehabilitation field, to estimate the TEP from the collected data during the DT VR experience. Based on our research question and available data we will use a classification algorithm to create a model; we will train and test the model using data to forecast which motor or cognitive parameters are more predictive for the future maintenance of any improvements obtained, based on the model proposed by Shi and colleagues (2019) [44]. We will use one of the best programs for ML analysis, such as Python.

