## Experimental design

The protocol aims to improve motor and cognitive deficits in patients with Parkinsonian Syndromes. A clinical examination will verify the inclusion and exclusion criteria. The eligible subjects will be assessed, and outcome measures will be collected (t0) by a trained physiotherapist and psychologist. The specialist who assesses participants will not train them. Patients will be then randomly assigned to a control or experimental group using a randomization sequence obtained from the website randomizer.org. The first group will complete the treatment as usual (TAU). Usually, training consists of a series of neuropsychological exercises delivered in paper and pencil modality, and classic motor activity, comprehending aerobic and anaerobic activities delivered thanks to bodyweight exercises on a stationary bike in an ordinary gym. The other one will complete a VR dual-task training protocol. Based on the evidence that exercise programs with shorter session duration and higher frequency may generate the best results [23], we propose 4–5 weeks of training of 10 sessions of 1 hour approximately, two times a week. Completed the 10 biweekly rehabilitation sessions a new assessment will be done (t1). The neuropsychological and motor assessment will be carried out before (t0), immediately after (t1) and 3 months after the end of the 10 sessions (t2) to evaluate the short/medium-term efficacy of the treatment. The chart of the trial design is presented in Fig 1. Patients must attend at least 8 out of 10 rehabilitation sessions as well as all the assessments for the treatment to be considered effective. All participants will sign the written informed consent.

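### The only stated treatment test, a 2-df group-by-time interaction with baseline as an outcome level, is valid but less efficient than adjusting for baseline, and alone gives no VR–TAU difference at t1 or t2

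*Protocol article*

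**What the plan says.** The Data analysis section sets a 2x3 design. It takes "population training (VR vs. TAU) as a between variable", and "assessment of training effect (pre-test, post-test, and follow-up) within variables". The treatment test is then given in one sentence: "A mixed ANOVA will be performed to investigate interaction effects between and within variables". The section states no baseline-adjusted analysis and no comparison of the arms at a particular time.

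The Experimental design section gives the order of events. First, "The eligible subjects will be assessed, and outcome measures will be collected (t0) by a trained physiotherapist and psychologist". Then, "Patients will be then randomly assigned to a control or experimental group using a randomization sequence obtained from the website randomizer.org". The assessment is repeated straight after the 10 sessions (t1) and 3 months later (t2), "to evaluate the short/medium-term efficacy of the treatment".

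The Participants section bases a final sample of 45 on a calculation "with an effect size of 0.43, alpha of 0.05, and 80% power". It names neither the effect-size metric nor the test.

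**The concern.** Baseline precedes randomisation, so the arms can differ at t0 only by chance. Making t0 a level of the outcome factor asks the data to estimate a group difference at t0 that is known to be zero in expectation. Using t0 as a covariate removes the same between-patient variation with less noise.

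The interaction has (2−1)(3−1) = 2 degrees of freedom. A significant result says that the two profiles differ somewhere over the three times. By itself it does not say at which time, in which direction or by how much. The stated aim is short- and medium-term efficacy, which calls for a difference at t1 and a difference at t2.

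What is at stake is efficiency and interpretability in a trial of 45 patients.

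**Working it through.** **Which effect size the plan's 45 implies.** For a two-group F test with f = 0.43 and N = 45, λ = 0.43² × 45 = 8.32 on 1 and 43 df, with power 80.5%; N = 44 gives 79.6%. So 45 reproduces with f = 0.43, which is d = 2 × 0.43 = 0.86 SD between two equal groups. It also reproduces as a paired t test with dz = 0.43. A two-sample t test with d = 0.43 would need 172. The metric is not stated, so both d = 0.43 and d = 0.86 are carried below.

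**Assumptions not in the documents.** Allocation 22/23, equal variances, compound symmetry with correlation ρ, complete data, two-sided alpha 0.05. The documents give no ρ, so a range is shown.

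**Interaction as planned.** With h = 22 × 23/45 = 11.24 and arm differences δ at t0, t1, t2:

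λ_int = h Σ(δ_t − mean δ)²/(1−ρ), on 2 and 86 df.

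- Sustained effect, δ = (0, d, d): Σ = (2/3)d².
- Halved at t2, δ = (0, d, d/2): Σ = (1/2)d².

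**Baseline-adjusted joint test of t1 and t2, also 2 df.** Given t0, each follow-up score has variance 1−ρ², and the two have covariance ρ−ρ². On 2 and 41 df:

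- Sustained: λ_adj = 2hd²/[(1−ρ)(1+2ρ)].
- Halved: λ_adj = hd²(1.25+0.25ρ)/[(1−ρ)(1+2ρ)].

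For a sustained effect λ_adj/λ_int = 3/(1+2ρ), which is 1.50, 1.25, 1.15 and 1.07 at ρ = 0.5, 0.7, 0.8 and 0.9.

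Example, d = 0.43, ρ = 0.5, sustained: λ_int = 11.24 × 0.667 × 0.1849/0.5 = 2.77, power 29%. λ_adj = 2 × 11.24 × 0.1849/(0.5 × 2) = 4.16, power 40%.

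Power, interaction vs baseline-adjusted, both 2 df:

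| Effect | ρ = 0.5 | ρ = 0.7 | ρ = 0.8 |
|---|---|---|---|
| d = 0.43, sustained | 29 vs 40% | 46 vs 53% | 63 vs 68% |
| d = 0.43, halved at t2 | 23 vs 29% | 35 vs 40% | 51 vs 54% |
| d = 0.86, sustained | 84 vs 95% | 97 vs 99% | about 100% for both |

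At ρ = 0.9 and d = 0.43 the two tests are level: 92% each if sustained, 82% each if halved. The adjusted figures ignore the cost of estimating the baseline slope. Multiplying λ_adj by (1 − 1/43) lowers them by about one point or less.

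**Size.** In null simulations the interaction test rejected 5.3% of the time, in line with its nominal 5%.

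**What a single-time contrast does.** The adjusted t1 contrast has λ = hδ₁²/(1−ρ²) on 1 and 42 df, where δ₁ is the t1 difference.

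- Effect of 0.43 SD at t1, halved at t2: 37, 51 and 65% at ρ = 0.5, 0.7 and 0.8, against 23, 35 and 51% for the interaction.
- Pattern reversed, the t1 effect being half of a 0.43 SD effect at t2: 13, 17 and 22%, against the same 23, 35 and 51%.

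**The case against.** The strongest defence is that a mixed ANOVA is a conventional and valid analysis of a randomised 2x3 design. Contrasts at t1 and t2, a sphericity correction and the reporting of estimates with intervals are commonly left to an analysis plan that is not shown. This stands for those details: their absence from the article is no error, and the article does not say that only a p-value will be reported. It does not answer the main point, because the article itself fixes baseline as an outcome level and the interaction as the test.

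The defence also limits the size of the point, and four stronger readings should be resisted.

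- A reader might quote the gap of about 14 to 15 points between the interaction and an adjusted t1 contrast when the effect fades. Most of that gap comes from choosing t1 in a scenario that favours t1. The like-for-like gain there is about 3 to 6 points.
- A reader might make t1 the main time. The documents never do, and the t2 assessment is part of the stated aim.
- A reader might call the trial underpowered for 0.43 SD. That presumes a metric the article does not state; 45 reproduces with f = 0.43, or 0.86 SD.
- A reader might say that chance imbalance at t0 makes the test produce false positives. Over all randomisations the test holds its 5% level, so this is not an error of the plan.

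**Conclusion.** The point holds as one of efficiency and interpretability, not of bias or validity. The stated test uses the pre-randomisation score less well than adjustment would, and on its own it does not deliver the t1 and t2 differences that the efficacy aim calls for.

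For an effect of 0.43 SD and ρ from 0.5 to 0.8, the like-for-like gain in power is about 5 to 11 points if the effect is sustained and about 3 to 6 points if it halves by t2. For 0.86 SD, sustained, it is about 11 points at ρ = 0.5 and 2 points or less from ρ = 0.7. It is about nil near ρ = 0.9. These sizes rest on the assumed correlation, compound symmetry and the 22/23 split. The case for estimating a difference at each time does not depend on them.

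**What to change.** Replace the mixed ANOVA by a linear mixed model on the t1 and t2 scores, with fixed effects for t0 score, arm, time, arm x time and t0 x time, and an unstructured covariance over the two times. Report the adjusted VR–TAU difference with its 95% CI at both t1 and t2. Name in advance which contrast is the main one: t1, t2, their mean or the joint test.

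The data are already planned, so the cost is rewording the Data analysis section before outcomes are analysed. There is one small downside: a single-time main contrast loses power if the effect lies mainly at the other time. The choice should therefore follow from the clinical question, and the joint test is available if neither time takes precedence.
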